### Eligibility of Participants

#### Inclusion Criteria

Pregnant women will be eligible if they are at least 18 years of age, have a singleton pregnancy according to ultrasonographic evaluation, are at 24-28 gestational weeks, have access to a mobile phone and the internet, and have SUI symptoms with ≥1 leakage episodes over the past 4 weeks (SUI symptoms are assessed by asking the question “When does urine leak?”). The question is an unscored item in the International Consultation on Incontinence Questionnaire-Urinary Incontinence Short Form (ICIQ-UI-SF), which has good reliability and validity [39]. SUI is defined as involuntary urine leakage on effort or physical exertion (eg, sports activities) or during sneezing or coughing [3]).

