### Measurements and Instruments of Data Collection

#### Overview

We will use a mixed-methods approach to evaluate the effectiveness and implementation of the trial according to the RE-AIM framework. Quantitative methods will be specifically used to measure the dimensions of Reach, Effectiveness, Adoption (UIW app usage results and patterns), Implementation, and Maintenance. For the Adoption dimension, qualitative methods will be used to explore the facilitators and barriers to adoption of the UIW app-based intervention from the pregnant women’s perspective. Multimedia Appendix 5 demonstrates the measures used in this study. Data will be collected at recruitment (–T1), baseline (T0), immediately after the intervention (T1), 42 days after delivery (T2), 3 months after delivery (T3), and 6 months after delivery (T4). Data will be collected from both the UIW app-based intervention group and control group. For the Reach dimension, the participation rate of eligible pregnant women will be examined using the project document data recorded by the researchers. For the Effectiveness dimension, there is 1 primary outcome, and there are 4 secondary outcomes, which are described in the following sections.

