### Data Management and Analysis

#### Quantitative Data

To avoid bias due to unnecessary face-to-face contact, data for pregnant women in both the intervention group and control group are collected electronically, using app-based and internet-based methods, respectively. After the data are exported from the app’s background management system and questionnaire website, data will be entered directly in a special database for the UIW app and saved in the database by researchers on a password-protected computer. Each participant is identified by a unique study ID assigned by the independent researcher assistant at the time of recruitment. And the “log” connecting the participants with the study IDs is held by the independent research assistant.

SPSS (version 25.0; IBM Corp, Armonk, NY) will be used for all quantitative data analysis. Descriptive statistics will be used to show continuous variables as mean (SD) and categorical variables as frequency and percentage. The baseline data will be compared between the intervention and control groups as well as between participants completing the follow-up of this study and those who drop out, with the independent sample *t* test for continuous variables and the chi-square test or Fisher exact test for categorical variables. The effects of the intervention within each group will be assessed with a paired *t* test for the severity of SUI, quality of life, and self-efficacy with PFMT and a McNemar chi-square test for risk factors. To compare the effects of the intervention between groups for the repeated measures, including severity of SUI, quality of life, and self-efficacy with PFMT, a linear mixed model will be used, which allows for missing data [57]. The model will include subjects as random effects and time, intervention, and the interaction between intervention and time as fixed effects. Pelvic floor muscle strength will be compared between groups using an independent sample *t* test. For the risk factors and PFMT adherence, chi-square tests will used to compare the differences between groups. *P* values <.05 will be considered statistically significant.

Participants with missing data will also be included in the analysis following the principle of intention-to-treat analysis. Missing data at follow-up will be replaced with the corresponding values at baseline.

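### With subject as the only random effect named, the mixed model as written assumes one variance and one correlation across all visits, so standard errors for visit-specific effects may be wrong in either direction

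*Protocol article*

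**What the plan says.** The Quantitative Data section of the protocol article applies the model to three repeated outcomes, "including severity of SUI, quality of life, and self-efficacy with PFMT, a linear mixed model will be used, which allows for missing data". It then lists the terms: "The model will include subjects as random effects", with time, intervention and their interaction as the fixed effects. It gives no residual covariance structure and no degrees-of-freedom method, and it does not say which visit-specific contrast will be tested. The software is SPSS 25.

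The Overview of measurements sets the schedule as baseline (T0), then "immediately after the intervention (T1), 42 days after delivery (T2), 3 months after delivery (T3), and 6 months after delivery (T4"). Women enter when they "are at 24-28 gestational weeks" (Inclusion Criteria), and the intervention lasts 2 months. The first two outcome visits are therefore planned about 2 months apart, starting in mid-pregnancy, and the last three follow birth. The section on secondary outcomes and RE-AIM measures assigns the Maintenance dimension to T2, T3 and T4.

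**The concern.** A subject random intercept with independent residuals is compound symmetry: equal variance at every visit and equal correlation for every pair. The article itself gives three reasons to doubt this.

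- **Spacing.** T0 to T1 is 2 months. T0 to T4 is roughly 9 months, if birth comes about 3 months after entry.
- **Delivery.** It lies between T0/T1 and T2-T4, and the Introduction puts SUI prevalence at about 40% in pregnancy and just over one-fifth after delivery.
- **Spread of scores.** Every woman must leak at entry, but women who recover can later score 0 on the 0-21 scale, so the variance may change over time.

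The model has one pooled residual variance for all contrasts. If the true covariance differs from compound symmetry, some visit-specific tests will be too conservative and others too liberal. The primary outcome is among those affected, and so are the late visits that would support a claim of a maintained effect.

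**Working it through.** **1. The plan's own figure.** With d = 0.344, two-sided alpha 0.05 and 134 per arm, the noncentral t gives power 0.801, so 268 reproduces. Then 268/0.80 = 335, or 336 in equal arms. This calculation uses no repeated-measures covariance, so the point does not touch it.

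**2. What the stated model implies.** Let the intercept variance be a and the residual variance e. Each visit then has variance a + e, and each pair of visits has covariance a.

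**3. What the fit reports.** The plan says "Missing data at follow-up will be replaced with the corresponding values at baseline", so the data set is balanced. With balanced data and a full time-by-group mean, the fitted model reports the average visit variance v and the average between-visit covariance c. Per woman:

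- Change from T0 to visit j: model variance 2(v − c); true variance v0 + vj − 2·c0j.
- Single visit j: model variance v; true variance vj.
- r = √(model/true); real type I error = 2·P(Z > 1.96·r).

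**4. Assumed inputs.** The documents give no standard deviations or correlations, so all of these are assumptions. Visit times are 0, 2, 4.7, 6.2 and 9.2 months, with birth about 3.2 months after entry. The SD is 1 at each visit unless stated.

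**5. Two worked cases.**

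*Correlation decaying at 0.80 per month.* T0-T1 correlation = 0.80^2 = 0.64; T0-T4 = 0.80^9.2 = 0.128; average over the ten pairs c = 0.410. Model variance of a change = 2(1 − 0.410) = 1.179.
- T1: true 2(1 − 0.64) = 0.720; r = 1.28; type I error 1.2%.
- T4: true 2(1 − 0.128) = 1.743; r = 0.82; type I error 10.7%.

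*SDs falling after delivery (1, 1, 0.8, 0.7, 0.6), equal correlation 0.5.* v = (1 + 1 + 0.64 + 0.49 + 0.36)/5 = 0.698.
- Single-visit difference at T1: r = √(0.698/1) = 0.835; type I error 10.2%.
- Single-visit difference at T4: r = √(0.698/0.36) = 1.39; type I error 0.6%.

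**6. Real type I error at nominal 5%.**

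| Assumed truth | Change, T1 | Change, T4 | Single visit, T1 | Single visit, T4 |
|---|---|---|---|---|
| Compound symmetry, 0.5 | 5.0% | 5.0% | 5.0% | 5.0% |
| Decay 0.80 per month | 1.2% | 10.7% | 5.0% | 5.0% |
| Decay 0.90 per month | 0.7% | 13.5% | 5.0% | 5.0% |
| 40% stable, 30% decaying at 0.80, 30% error | 3.4% | 7.1% | 5.0% | 5.0% |
| 0.7 within and 0.4 across delivery | 1.3% | 8.0% | 5.0% | 5.0% |
| Falling SDs, correlation 0.5 | 9.4% | 5.5% | 10.2% | 0.6% |

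A sharper assumed SD pattern (1, 1.2, 1, 0.8, 0.6) takes the single-visit error at T4 down to 0.2%.

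**7. Simulation check.** The formula was tested with 150 simulated fits at N = 268, with a correlation of 0.7 between successive visits. For T4 change, the empirical SD was 0.157 against a model SE of 0.119, with 14% rejections (formula 11.9%). For T1 change, it was 0.088 against 0.119, with 0% rejections (formula 1.3%).

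**8. Power at T1.** For a change of 0.344 SD with 134 per arm, power falls from 0.91 to 0.79 at decay 0.80, but only from 0.995 to 0.969 at decay 0.90.

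**The case against.** The strongest reply is that the article never says the random intercept is the only correlation structure. SPSS can fit a residual covariance alongside or instead of a random effect, and covariance structure, degrees of freedom and convergence rules usually belong in an analysis plan, which is not shown. This stands in part: the missing degrees-of-freedom method and fallback are no fault in an article. It is not a full answer, because the article does list the model's terms. An analyst who follows that list fits a random intercept with independent residuals, and the schedule makes that structure doubtful.

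A reader might go further and infer that the standard errors will be wrong, too wide at the end of the intervention and too narrow late after birth. The documents do not support that:

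- If compound symmetry holds, every standard error is right.
- With equal variances, single-visit group differences are unaffected at every visit.
- If SDs fall after delivery, the direction reverses for single-visit differences: liberal at T1 and conservative at T4.
- A mix of stable, decaying and error variance shrinks the effect on changes to 3.4% at T1 and 7.1% at T4.
- The article does not say which contrast it will test.

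Nor is a serious loss of power shown: in the decay cases examined, T1 power stays at about the planned 0.80 or above.

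Replacing missing values with baseline values would itself alter the visit variances and correlations. That is a separate matter.

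**Conclusion.** The point holds as a conditional one. As written, the model fixes one variance and one correlation for all visits over a period in which both are doubtful. If they are not constant, intervention-by-time contrasts can have wrong standard errors, and single-visit differences can too where variances differ. Over the tabulated assumptions the real type I error runs from about 0.6% to 13.5%, and it is exactly 5% if compound symmetry holds. These figures rest on assumed covariances, assumed visit times and balanced data. The sample size of 336 is unaffected. This is a weak choice with an inexpensive better alternative, not a demonstrated error.

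**What to change.** State that the repeated outcomes will be analysed with an unstructured residual covariance over T0-T4, in place of the random intercept (in SPSS MIXED: REPEATED by subject, COVTYPE(UN)), with Satterthwaite degrees of freedom. Name one fallback in advance in case the model does not converge: either heterogeneous Toeplitz or heterogeneous first-order autoregressive. Both let the variance differ by visit, though both treat successive visits as equally spaced. The fixed effects stay as they are.

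The cost is one line of text and syntax and no extra data. Five visits need 5 × 6/2 = 15 covariance parameters instead of 2, a small load for 336 women, and little is lost if compound symmetry turns out to be true. The change should be recorded before outcomes are compared by group.

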#### Sample Size Calculation

The sample size calculation was based on the primary outcome of the SUI symptom score, which is used to estimate the effect size in the power analysis [58]. A previous mobile app–based study performed among primiparas women showed a moderate effect size (0.344) [25]. G*Power [59] was used to estimate the sample size. A minimum sample size of 268 pregnant women is required for this study to achieve a power of 0.80 at a 2-sided significance level of .05. A 20% attrition rate is estimated based on previous studies involving mHealth interventions [60]. The total sample size was increased to 336, with 168 in each group.

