### Strengths and Limitations

This study is powered by some strengths. First, the UIW app functions are comprehensive. It not only focuses on PFMT but also merges various behavior change techniques, including shaping knowledge, feedback, self-monitoring, and others [40]. Second, given the implementation of “Two-Child Policy” in China, the number of multiparas women is obviously increasing [62]. To evaluate the effectiveness of the UIW app-based intervention in a more realistic clinical context, we will enroll both primiparas and multiparas women in this study. Third, a hybrid type 1 effectiveness-implementation design, with RE-AIM as the guidance framework, is applied in this study. The RE-AIM framework specifies multiple domains of evaluation [34] and has been commonly utilized in research on health promotion intervention [63]. Knowledge gained from this sophisticated design will make a great contribution to the RCT evaluating the mHealth intervention. Furthermore, integration of quantitative and qualitative methods will occur at various levels through the mixed-methods design of the implementation evaluation [32]. At the study design level, an explanatory sequential design is employed. In the qualitative study, interview samples will be purposely selected from the participants of the RCT according to the primary outcome. Thus, integration occurs through connecting and building at the methods level.

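### The mixed model for the primary outcome neither adjusts for the baseline score nor holds the arms to a common baseline mean, which loses precision by an amount that depends on an unstated correlation

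*Protocol article*

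**What the plan says.** Under Data Management and Analysis (Quantitative Data), the between-group comparison of SUI severity, quality of life and PFMT self-efficacy is a linear mixed model. Subjects are random, with "time, intervention, and the interaction between intervention and time as fixed effects". The section does not say whether T0 is one of the responses, or which term or visit is the primary contrast.

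The T0 score will be available. The Overview of the measurements lists T0 as a collection time, and the same analysis section relies on baseline values for the within-group paired tests and for replacing missing follow-up values.

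The Sample Size Calculation section takes a single standardised effect of 0.344 from an earlier app study. It states "A minimum sample size of 268 pregnant women is required for this study to achieve a power of 0.80", allows for 20% attrition, and concludes "The total sample size was increased to 336, with 168 in each group". It uses no correlation and no baseline adjustment, and does not say whether 0.344 was standardised on follow-up scores or on change.

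**The concern.** The fixed effects are given as a closed list, and that list makes poor use of a baseline measurement of the primary outcome. There are two readings:

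- **T0 is a response.** Each arm gets its own T0 mean, and the interaction at a follow-up visit is the between-arm difference in change from baseline.
- **T0 is left out.** The between-arm difference at a visit is a comparison of follow-up scores that ignores baseline.

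Both are valid under randomisation. Both are less precise than an analysis that conditions on the T0 score or assumes, as randomisation justifies, that the arms share one T0 mean. At stake are wider confidence intervals than the data require and, in some circumstances, less power than the 0.80 planned.

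**Working it through.** **Inputs from the protocol article.** Standardised effect d = 0.344, two-sided alpha 0.05, power 0.80, minimum total 268 (134 per arm), attrition 20%, total 336 (168 per arm), and the model terms given above.

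**Assumptions not in the document.** The correlation rho between the T0 score and a follow-up score is taken as 0.3 to 0.7. Variances are equal at T0 and follow-up. The effect d is in units of the follow-up-score SD.

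**The plan's own figure.** The normal approximation gives n per arm = 2(1.96 + 0.8416)² / 0.344² = 2 × 7.849 / 0.1183 = 132.7, so 133. The exact two-sample t test gives 134 per arm, total 268, power 0.801. Attrition: 268 / 0.80 = 335, made even as 336. The stated figures are reproduced for an unadjusted two-group comparison.

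**Variance of each contrast at one visit, in units of the outcome variance.**

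- Change from baseline: 2(1 − rho)
- Follow-up only: 1
- Baseline-adjusted: 1 − rho²

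The change variance exceeds the adjusted one by 2(1 − rho) − (1 − rho²) = (1 − rho)². The follow-up-only variance exceeds it by rho². Both excesses are positive for any rho strictly between 0 and 1. The share of information lost is (1 − rho)/2 for change and rho² for follow-up only.

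**Power.** Power ≈ Φ(d√(n/2v) − 1.96), where v is the variance above. With n = 134, d√(n/2) = 0.344 × √67 = 2.816. For example:

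- Follow-up only: Φ(2.816 − 1.96) = Φ(0.856) = 0.804
- Change, rho 0.3: Φ(2.816/√1.40 − 1.96) = Φ(0.420) = 0.663
- Adjusted, rho 0.3: Φ(2.816/√0.91 − 1.96) = Φ(0.992) = 0.839

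| rho | Lost, change | Lost, follow-up only | Power, change | Power, follow-up only | Power, adjusted | Total N for 0.80, change | Total N for 0.80, adjusted |
|---|---|---|---|---|---|---|---|
| 0.3 | 35% | 9% | 0.66 | 0.80 | 0.84 | 372 | 242 |
| 0.4 | 30% | 16% | 0.73 | 0.80 | 0.87 | 320 | 224 |
| 0.5 | 25% | 25% | 0.80 | 0.80 | 0.90 | 266 | 200 |
| 0.6 | 20% | 36% | 0.88 | 0.80 | 0.94 | 214 | 170 |
| 0.7 | 15% | 49% | 0.95 | 0.80 | 0.98 | 160 | 136 |

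The totals use the normal approximation, so 266 is the counterpart of the plan's 268. Change-score power reaches 0.80 at rho of about 0.50 with 134 per arm, or about 0.37 if all 168 per arm are observed.

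**Check on the model itself.** In one simulated data set (134 per arm, five visits, rho 0.5), the stated random-intercept model with T0 as a response gave a T1 interaction of −0.4169. This equals the raw difference in mean change. Holding the T0 means equal cut the standard error from 0.1205 to 0.1057, a variance ratio of 0.77. That is a reduction of about 23%, close to the 25% in the table.

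**The case against.** The strongest reply is that time, intervention and their interaction with a random subject effect is a standard and unbiased analysis of a randomised longitudinal trial. With T0 as a response, which is the natural reading of repeated measures, the baseline scores are used. Detail is also commonly left to an analysis plan that is not shown here. The first two points stand: there is no bias, and on that reading baseline is not ignored. They do not restore the precision lost by giving the arms separate T0 means. Nor is this a matter of omitted detail, since the article states which fixed effects the model contains.

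A reader might infer more than the document supports:

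- **That the trial is underpowered.** This needs a single-visit change contrast, rho below about 0.5, and 0.344 standardised on follow-up scores. If 0.344 was standardised on change, the stated power already applies to a change test. A follow-up-only test keeps 0.80. If the four follow-ups are averaged, with the same effect at each visit and the same correlation between all visits, change-score power at 134 per arm is 0.853 at rho 0.3 and 0.945 at rho 0.5.
- **That rho must be low because follow-up extends past delivery.** Women enter at 24 to 28 weeks and the intervention lasts 2 months, so T1 normally falls in late pregnancy. No figure in the document places rho below 0.5.
- **That one fixed share of information is wasted.** A figure such as 25% to 35% fits a change contrast only at rho 0.3 to 0.5.
- **That parity must be in the model.** The Strengths and Limitations section says "we will enroll both primiparas and multiparas women in this study", but randomisation is simple and unstratified, and no gain from adjusting for parity can be computed from the document. It is optional.

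Enrolling 336 does not by itself remove the concern. If 20% of follow-up scores are replaced by baseline, the effect shrinks to 0.8 × 0.344 = 0.275 and the change variance to about 0.8 of its value. Then 168 per arm is worth about 0.8 × 168 = 134.4 per arm, and change-score power is again about 0.66 at rho 0.3 and 0.73 at rho 0.4.

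**Conclusion.** The point holds as one of efficiency. As fixed in the article, the model loses precision that baseline scores already collected would supply. The ordering of the three variances needs only equal variances and a correlation strictly between 0 and 1.

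The size rests on a rho that the document does not give. Over 0.3 to 0.7, baseline adjustment raises single-visit power at 134 per arm from 0.66–0.95 (change) or 0.80 (follow-up only) to 0.84–0.98. These figures also assume that 0.344 is on the follow-up-score scale.

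It would go too far to conclude that the sample size is wrong or the estimate biased. The figures 268 and 336 are correct for the comparison they were built on, and randomisation protects the estimate under either reading.

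**What to change.** State whether T0 is a response, name the primary contrast (which visit, or which average of visits), and prespecify one of two models:

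1. Keep T0 as a response and give both arms a common T0 mean: time plus intervention-by-visit terms for T1 to T4, with no intervention term at T0.
2. Model T1 to T4 as responses, with the T0 score and its interaction with time as covariates.

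The two need not coincide exactly under a random-intercept structure, so one should be chosen in advance. Apply the same choice to IIQ-7 and BPMSES.

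The cost is a sentence or two in the analysis plan, written before outcomes are compared by arm. No extra data or participants are needed.

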#### Secondary Outcomes

The secondary outcomes include pelvic floor muscle strength, quality of life, self-efficacy with PFMT, and risk factors for SUI.

Pelvic floor muscle strength will be assessed using sEMG with the Vishee neuro-muscle stimulator (MyoTrac Infiniti, model SA9800, Thought Technology Ltd, Montreal, Quebec) [50]. It will be performed by following the Glazer protocol by 2 independent and experienced obstetricians who have passed the medical qualification examination and have more than 5 years of working experience. After participants are in a supine lithotomy position, a drop-shaped vaginal probe (registration certificate number: 20152211142, type VET-A, produced by Nanjing Vishee Medical Technology Ltd, Nanjing China) will be placed into the vagina. Participants will be instructed how to correctly contract the pelvic floor muscles to avoid crosstalk contamination of the surrounding muscles before starting the test. Then, participants will follow the text hints and voice prompts of the automated protocol software to contract and relax the pelvic floor muscles. The whole test includes 5 indicators of amplitude (µV): pretest resting, phasic contraction, tonic contraction, endurance contraction, and posttest resting. A lower amplitude indicates weaker pelvic muscle strength. sEMG is a reliable way to measure pelvic floor muscle strength, and its values are closely related to SUI [51].

Quality of life among pregnant women with SUI will be assessed using the Incontinence Impact Questionnaire-7 (IIQ-7) [52]. The IIQ-7 is a 7-item instrument with 4 domains including physical activity, travel, social activities, and emotional health. Higher total score indicates a higher level of impact on life. The Chinese version of the IIQ-7 has a Cronbach α coefficient of 0.824 and high construct validity [53].

Self-efficacy with PFMT will be measured using the Broome Pelvic Muscle Self-Efficacy Scale (BPMSES) [54]. The BPMSES is a 23-item instrument with 14 items in the dimension of self-efficacy expectations and 9 items in the dimension of outcome expectations. A total score of 0-33 indicates low self-efficacy, 34-66 indicates moderate self-efficacy, and 66-100 indicates high self-efficacy. The Chinese version of the BPMSES has a Cronbach α coefficient of 0.912 and a test-retest reliability coefficient of 0.910 [55].

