Risk factors for SUI among pregnant women will be assessed using a self-designed questionnaire, investigating weight, condition of constipation, active and passive smoking, and consumption of liquids containing caffeine.

For the dimension of Adoption, the pregnant women’s PFMT adherence and activity in the 2 groups, usage results and patterns of use of the UIW app for the intervention group, other possible apps and websites used by the control group, and facilitators and barriers to adoption of the app will be explored through quantitative and qualitative methods. PFMT adherence and activity as well as usage results and patterns will be evaluated using quantitative methods through the log data of the background management system for the intervention group; a self-administered, electronic PFMT diary; and an electronic questionnaire (Multimedia Appendix 5). For the qualitative interviews, we will adopt a purposive sampling strategy to select women from the 2 groups based on the primary outcome of the SUI symptom score at the end of the intervention. Pregnant women will be selected at a ratio of 1:1 in the higher and lower scores until achieving data saturation such that no new themes emerge during data analysis. The interviews will be performed by a researcher ([name]) via telephone or face-to-face. The interviewer is a female nurse with a master’s degree in nursing science and formal training in qualitative studies. A semistructured interview guide was developed by the research team and covers the topics of user experiences, preferences, and expectations (Multimedia Appendix 5). Data collection, management, and analysis will be carried out concurrently, which makes it possible to adapt and refine the interview guide [56]. All interviews were audiotaped after gaining permission from the participants.

For the dimension of Implementation, the fidelity of the intervention and usual care provided will be evaluated (Multimedia Appendix 5).

For the dimension of Maintenance, the measures used to assess “Effectiveness,” “Adoption,” and “Implementation” will be repeatedly assessed in the follow-up period at the T2, T3, and T4 time points.

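### Risk factors for SUI are compared between groups only by chi-square, which requires weight to be categorised and leaves the T0 and repeated values unused

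*Protocol article*

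**What the plan says.** All of the relevant text is in the protocol article.

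- **The outcome.** The Secondary Outcomes section states: "The secondary outcomes include pelvic floor muscle strength, quality of life, self-efficacy with PFMT, and risk factors for SUI". Risk factors are collected with a self-designed questionnaire "investigating weight, condition of constipation, active and passive smoking, and consumption of liquids containing caffeine".
- **The schedule.** The same section says, for the Maintenance dimension, that the effectiveness measures "will be repeatedly assessed in the follow-up period at the T2, T3, and T4 time points".
- **The within-group test.** The Quantitative Data section assigns "a McNemar chi-square test for risk factors".
- **The between-group test.** The same section states: "For the risk factors and PFMT adherence, chi-square tests will used to compare the differences between groups". It names no time point for this test and gives no categories for weight.
- **The other repeated outcomes.** The same section says that, "for the repeated measures, including severity of SUI, quality of life, and self-efficacy with PFMT, a linear mixed model will be used", with subject as a random effect and time, intervention and their interaction as fixed effects. Risk factors are not on that list.
- **Baseline comparisons.** Here the section separates variables by type, "with the independent sample *t* test for continuous variables and the chi-square test or Fisher exact test for categorical variables".

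**The concern.** Chi-square and McNemar are both tests for categorical data, and they are the only tests assigned to risk factors. If the questionnaire records weight as a number, the planned test can be run only after grouping it, which discards information. Elsewhere in the same section the plan gives continuous variables a *t* test.

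Whatever the scale of each factor, the between-group chi-square compares the arms without using what is known about each woman at T0 and without combining her later assessments. McNemar does not fill that gap. It is paired, but it describes change inside one arm. T0 falls at 24-28 weeks of gestation and T2 to T4 fall after delivery, so within-arm change in weight between those points will largely reflect pregnancy and birth. Only the between-group comparison can show an effect of the app.

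Weight management and constipation prevention are among the app's health-education topics. Usual care covers the same five topics verbally in both arms, so any difference between arms may be small. At stake is the precision of one secondary outcome.

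**Working it through.** **1. The plan's own figure.** The Sample Size Calculation uses effect size 0.344, power 0.80 and two-sided alpha .05. The Randomization and Blinding section gives 1:1 allocation. A two-sample *t* test needs 133.6 per arm, so 134 per arm and 2 × 134 = 268 in total. With 20% attrition, 134 / 0.8 = 167.5, so 168 per arm and 336 in total. Both stated figures reproduce, and this point does not dispute them.

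**2. What categorising weight could cost.** The documents give no SD, expected effect or cut-off for weight. The assumptions, for illustration only, are: weight is normal; the app lowers it by 0.344 SD (a figure borrowed from the SUI score); 134 women per arm are analysed.

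- Continuous comparison: 0.344 / √(2/134) = 2.816; power = Φ(2.816 − 1.96) = 0.80.
- Chi-square after a cut at c SD above the control mean: p1 = 1 − Φ(c), p2 = 1 − Φ(c + 0.344); power = Φ{[(p1 − p2) − 1.96 √(2p̄(1 − p̄)/n)] / √([p1(1 − p1) + p2(1 − p2)]/n)}, where p̄ is the mean of p1 and p2 and n = 134.
- Efficiency relative to the continuous analysis: φ(c)² / [p1(1 − p1)]. At the median this is 2/π = 0.64.

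| Controls above the cut (p1) | App arm (p2) | Power of chi-square | Relative efficiency |
|---|---|---|---|
| 50% | 36.5% | 0.61 | 0.64 |
| 30% | 19.3% | 0.53 | 0.58 |
| 20% | 11.8% | 0.45 | 0.49 |
| 10% | 5.2% | 0.32 | 0.34 |

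With all 168 per arm analysed, the continuous comparison has power 0.88, against 0.70, 0.63, 0.54 and 0.38 for the same four cuts. The ordering also holds for other assumed shifts. With 134 per arm, a shift of 0.2 SD gives 0.37 continuous against 0.25 at the median cut, and 0.5 SD gives 0.98 against 0.90.

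**3. What leaving out T0 could cost.** Adjusting a continuous outcome for its baseline multiplies the variance by 1 − ρ², where ρ is the correlation between T0 and follow-up. The documents give no ρ, so a range is assumed.

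- ρ = 0.5: 1 − 0.25 = 0.75, a 25% reduction. Power = Φ(2.816/√0.75 − 1.96) = 0.90.
- ρ = 0.7: 1 − 0.49 = 0.51, a 49% reduction. Power = 0.98.
- ρ = 0.9: 1 − 0.81 = 0.19, an 81% reduction. Power is above 0.99.

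**4. Repeated assessments.** Nothing numerical is needed here. The Secondary Outcomes section has the effectiveness measures reassessed after delivery, and the Quantitative Data section gives three of those outcomes a model with a group-by-time term. For risk factors, the between-group test is one that cannot take in more than one assessment per woman.

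**The case against.** The strongest reply is that weight may not be recorded as a number. Neither the self-designed questionnaire nor Multimedia Appendix 5 is shown. Giving categorical tests to every risk factor would be consistent with weight being collected in classes, and category definitions may properly sit in the appendix or full plan. This stands: the loss from grouping is conditional on how weight is recorded, and the missing cut-off is not itself a fault. It does not touch the unused T0 and repeated values, which are lost on either scale.

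A reader might infer several stronger points that the document does not support:

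- **That the whole analysis ignores baseline.** McNemar is paired and uses two values per woman. The criticism applies to the between-group chi-square.
- **That a cut-off for weight would be chosen after seeing the data.** Nothing in the text says so.
- **That a separate chi-square test is planned at every visit.** No time point is named.
- **That the chi-square test is wrong.** In a randomised trial an unadjusted comparison of a categorical outcome is valid. The issue is efficiency.
- **That the weight contrast isolates something only the app provides.** Usual care covers the same topics in both arms.

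It is also fair to say that the magnitudes are not specific to this trial. The 0.344 belongs to the SUI score, no median split is proposed, and one constant correlation from mid-pregnancy to six months after birth is doubtful. The figures show the direction and plausible range of the loss, and do not estimate it.

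**Conclusion.** The point holds in a limited form. For the risk-factor outcome the protocol article fixes a between-group test that requires weight in categories and uses neither T0 nor the repeated assessments, while three other repeated outcomes get a mixed model. The result would be valid but less precise than the data already being collected allow.

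Under the assumptions above, grouping weight would take power from 0.80 to between 0.61 and 0.32, depending on the cut. Using baseline would remove 25% to 81% of the variance. The first of these applies only if weight is recorded numerically. The schedule rests on the general statement about effectiveness measures, because the per-measure list is in the appendix; that T0 values exist follows from planning a paired test.

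This is a worthwhile improvement to one of four secondary outcomes. It does not affect the primary analysis or the 336 women.

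**What to change.** - **Weight, if recorded as a number:** analyse it as continuous in a linear mixed model with group, time and group-by-time, adjusted for T0 weight. The mixed model now described names no baseline covariate, so the T0 term has to be added explicitly.
- **Constipation, active and passive smoking, caffeine, and weight if recorded in categories:** use a repeated-measures logistic model, such as GEE, with group, time and their interaction, adjusted for the T0 value.
- **Chi-square:** keep it for descriptive tables.

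The cost is a little extra analysis in the software already named, with no further data collection. The drawback is that rare factors, active smoking being the likely one, may be too sparse for a stable model. For those a simple descriptive comparison can be kept.
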